#### Randomization and blinding

2.5.3

A total of 320 participants will be randomly assigned by a central computer randomization software program; 160 participants in the intervention group and 160 participants in the control group. The randomization sequence is automatically generated when the researchers complete the clinical evaluation and input the electronic data capture system (EDC), and artificial intervention is impossible.

This study is a single-blind trial design. Considering that the study needs the cooperation of participants and multi-disciplinary intervention teams, it is not possible to blind participants and staff administering interventions to group allocation. However, the staff performing the clinical evaluations, outcome assessors and data analysts will be blinded to the intervention group assignment. Assessors will not be involved in intervention activities.

#### Bias control

2.5.4

The endpoint events of this study are all objective indicators. Researchers will quantify these objective indicators and establish unified and clear criteria. The assessors will receive unified and standardized training before investigation. Through brief telephone reviews and record books, a good trust relationship with participants will help reduce selection bias and increase compliance.

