**Methods::**

In this study, 320 in patients with frailty ≥70 years old will be randomly divided into an intervention group and a control group. The intervention group will be given routine management, a CGA and multi-disciplinary management involving rehabilitation exercise, diet adjustment, multi-drug evaluation, acupoint massage in TCM and patient education for 12 months, and the control group will be followed up with routine management for basic diseases. The primary outcomes are the Fried phenotype and short physical performance battery (SPPB). The secondary outcomes are the clinical frailty scale (CFS), non-elective hospital readmission, basic activities of daily living (BADL), 5–level European quality of life 5 dimensions index (EQ-5D), nutrition risk screening-2002 (NRS-2002), medical insurance expenses, fall events, and all-cause mortality. In addition, a cost-effectiveness study will be carried out.

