### Study design and setting

2.1

This is a multicenter, randomized, parallel controlled study. The study has been designed to determine the effect of a CGA and multi-disciplinary management on patients ≥70 years old with frailty in China.

The primary outcomes are the Fried phenotype,^[1]^ which presenting at least 3 of the following: unintentional weight loss, self-reported exhaustion, weakness, slow walking speed and low physical activity; and the short physical performance battery (SPPB), scored from 1 to 12 based on three tests (balance tests, gait speed and 5-sit-to-stand test; low score 0–6, medium score 7–9, high score 10–12).^[32]^ The secondary outcomes are the clinical frailty scale (CFS), which uses pictographs and clinical descriptions to help clinicians stratify elder adults on a 9-point scale (1 being very fit and 9 being terminally ill);^[33]^ non-elective hospital readmission,^[13]^ which is considered any type of emergency readmission; disability, which is assessed by basic activities of daily living (BADL: total score 6);^[34]^ health-related quality of life, which is evaluated by the 5–level European Quality of Life 5 Dimensions index (EQ-5D: index values range from 0 to 1, with higher scores indicating a better quality of life);^[12]^ medical insurance expenses; fall events; nutrition risk screening-2002 (NRS-2002: the total score ranges from 0 to 7, and a total score ≥3 indicates malnourishment),^[35]^ and all-cause mortality.^[36]^ A standard multiplication model will be used to estimate the quality adjusted life years (QALYs), which are calculated based on the EQ-5D or BADL.^[37]^ The enrollment, intervention allocation, follow-up and data analysis will be conducted according to the Standard Protocol Items: Recommendations for Interventional Trials (SPIRIT) statement.^[38,39]^

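### Section 2.5.4 calls all endpoints objective, but the co-primary Fried count includes exhaustion reported by unblinded participants, and the two-outcome success rule covers this only in part

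*Protocol article*

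**What the plan says.** Section 2.5.4 (Bias control) makes a general claim: "The endpoint events of this study are all objective indicators". It then promises uniform criteria and adds "The assessors will receive unified and standardized training before investigation".

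The Abstract names two primary outcomes: "The primary outcomes are the Fried phenotype and short physical performance battery (SPPB". Section 2.1 gives the five Fried criteria as "unintentional weight loss, self-reported exhaustion, weakness, slow walking speed and low physical activity". It describes SPPB as scored "based on three tests (balance tests, gait speed and 5-sit-to-stand test". Among the secondary outcomes it lists EQ-5D for health-related quality of life, and the CFS, a nine-point scale on which clinicians grade the patient.

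On blinding, section 2.5.3 concedes that "it is not possible to blind participants and staff administering interventions to group allocation". It also provides that "the staff performing the clinical evaluations, outcome assessors and data analysts will be blinded to the intervention group assignment", and that "Assessors will not be involved in intervention activities".

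Section 2.8 accepts the trial hypothesis only if both Fried and SPPB show superiority, at a two-sided 5% level. Section 2.6 lists SPPB among the rehabilitation assessments made in the intervention group.

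**The concern.** The sentence claims a property that one primary outcome does not have. Exhaustion is one of the five Fried criteria, and the protocol itself calls it self-reported. The person reporting it knows whether they received twelve months of exercise, diet, medication and massage advice. A blinded assessor records that answer faithfully, including any part that comes from expectation. EQ-5D has the same weakness, and the CFS depends on judgement.

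What is at stake is how firmly an improvement in frailty can be claimed. A difference in the Fried count could come partly from how participants answer one question. A text that calls every endpoint objective gives the reader no reason to check.

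**Working it through.** **1. The texts side by side.** Section 2.5.4 says all endpoints are objective. Section 2.1 puts a self-reported item inside a primary outcome and lists a quality-of-life report and a clinician's rating as secondary outcomes. Section 2.5.3 leaves participants unblinded. These statements cannot all stand. Reading the sentence as covering only death and readmission does not rescue it. It says all, and the text around it concerns uniform criteria and trained assessors.

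**2. Inputs for the size.** Section 2.4 plans Fried differences of 1.6 − 1.2 = 0.40 criteria (125 per group) and 0.80 − 0.41 = 0.39 criteria (128 per group), and an SPPB difference of 1.44 points (101 per group), with 80% power and 15% attrition from 160 per group. It gives no SD, so the per-group sizes cannot be reproduced independently. They can be solved for the SD they imply:

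SD = d / [(1.960 + 0.842) × √(2/n)]

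- Fried, d = 0.40, n = 125: SD = 1.129
- Fried, d = 0.39, n = 128: SD = 1.114
- SPPB, d = 1.44, n = 101: SD = 3.65

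Completers: 160 × 0.85 = 136 per arm.

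**3. Smallest significant Fried difference.** SE = 1.129 × √(2/136) = 0.137, and 1.96 × 0.137 = 0.268 criteria. If exhaustion alone produced this, the arms would have to differ by about 27 percentage points in reporting it.

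**4. Effect of a smaller false shift.** The size of the reporting difference is an assumption, so it is varied. One item answered x points less often in the intervention arm shifts the mean count by x/100. With no true Fried effect, the chance of significance in favour is 1 − Φ(1.96 − shift/0.137).

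| Reporting difference on exhaustion | Shift (criteria) | Share of planned 0.39 | P(Fried significant in favour) |
|---|---|---|---|
| 0 points | 0 | 0% | 2.5% |
| 5 points | 0.05 | 13% | 5.5% |
| 10 points | 0.10 | 26% | 11% |
| 15 points | 0.15 | 38% | 19% |
| 20 points | 0.20 | 51% | 31% |

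With all 160 per arm the 10-point row becomes 12%.

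**5. The success rule when SPPB has no effect.** Both outcomes must be significant, so the joint rate cannot exceed SPPB's own 2.5%, provided SPPB is unbiased. Simulation with correlations of 0 to 0.7 between the two test statistics gave 0.3% to 1.7% for a shift of 0.10 and 0.8% to 2.3% for a shift of 0.20.

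**6. The success rule when SPPB improves as planned.** Power for 1.44 points at SD 3.65 and 136 per arm is 90%. If the two tests are independent, the false joint claim is 0.109 × 0.902 = 10% for a shift of 0.10 and 0.309 × 0.902 = 28% for a shift of 0.20. Without any shift it is 0.025 × 0.902 = 2.3%. Positive correlation raises these figures, but never above Fried's own rate in step 4.

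**The case against.** The strongest reply is the success rule. A reader might infer that a positive trial could be nothing but reporting bias. Section 2.8 does not allow that inference: SPPB must also win, and it consists of physical tests. Step 5 shows the joint error held at or below 2.5% when SPPB has no effect. This part of the reply stands. It does not cover the case in step 6, where SPPB improves and Fried does not.

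The second reply is that bias control does not rest on this one sentence. Randomization is central, assessors and analysts are blinded, and assessors are trained and kept apart from the intervention. Unblinded participants are unavoidable with exercise, diet and massage, and the protocol says so openly. All of this stands, but none of it reaches the content of a participant's own answer.

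Three further inferences are tempting and not supported:

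- **Three self-reported Fried items.** Counting weight loss and physical activity as well would triple the 10-point shift to 0.30 criteria (77% of 0.39). The protocol calls only exhaustion self-reported and does not say how the other two are measured.
- **No check has been planned.** The analysis plan is not shown and may contain item-level or supportive analyses.
- **SPPB is inflated by extra or unblinded testing in the intervention arm.** Section 2.6 lists SPPB in the intervention group's rehabilitation assessment, and Table 1 ticks the CGA at every visit. However, the note to the asterisk on that row is not in the available text, and section 2.5.3 keeps outcome assessors out of the intervention. The source of the outcome score needs stating; a practice effect is not shown.

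**Conclusion.** The objectivity statement is wrong on the protocol's own definitions and should be corrected. The consequence is moderate. Reporting bias in Fried alone cannot readily make the trial positive, but it can distort the Fried estimate, and it can supply the second win when SPPB truly improves.

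On the assumptions used, a 10-point reporting difference on exhaustion raises Fried's favourable false-positive rate from 2.5% to about 11%. The false joint claim is then about 10% when SPPB performs as planned. Exhaustion alone would need a difference of about 27 points to bring the expected Fried difference up to the significance threshold.

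These figures rest on an SD that the document does not state (about 1.13, solved from the sample size), 136 completers per arm, an assumed reporting difference, and a simple comparison of two means. If the planned covariance analysis reduces residual variance, the same shift would be significant somewhat more often. The contradiction between the sections depends on none of these assumptions.

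**What to change.** 1. Replace the sentence in section 2.5.4 with two lists. Measured outcomes would include the SPPB, gait speed, death and readmission. Reported or judged outcomes would include exhaustion, EQ-5D, the CFS and any other Fried item scored from the participant's account. State that assessor blinding does not protect the reported outcomes.
2. Pre-specify, unless the analysis plan already does, a supportive covariance analysis of the Fried count without exhaustion and without any other item found to be scored from the participant's account. Report each of the five items by arm.
3. State that the frailty conclusion will be qualified if this analysis does not point in the same direction as the primary one. The success rule in section 2.8 need not change.
4. State that the outcome SPPB is the blinded assessor's score, since section 2.6 lists the same test in the intervention team's assessment.

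The Fried items have to be scored anyway to obtain the count, so this needs text and one extra model, with no new data or visits. It can be done while recruitment is under way, before analysis. The only downside is a slightly more guarded claim.

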### Intervention

2.6

Participants in the intervention group will receive a CGA and receive 12 months multi-disciplinary management. Interventions will be carried out by a multi-disciplinary team (including physicians, nurses, nutritionists, rehabilitation physicians, pharmacists, TCM physicians). A brief CGA will be carried out by nurses during the three days of hospitalization, including evaluations of the following data: hearing impairment, visual impairment, masticatory disorder, risk of fall and imbalance, history of falls, urinary incontinence and fecal incontinence, chronic constipation, and chronic pain. The specialized CGA and interventions are as follows:

1.Nutrition aspectAssessment: Age, grip strength, daily physical activity, NRS-2002 score, clinical diagnosis (especially sarcopenia), laboratory results, human body composition analysis (Inbody 720), dietary survey.Advice: A reasonable dietary plan will be formulated by the nutritionist.2.RehabilitationAssessment: SPPB, physical fitness tests,^[46]^ including a 30-second sit-to-stand test^[47–49]^ to assess lower body strength, a 30-second arm curl test^[50]^ to assess upper body strength, a 2-minutes step test^[51]^ to assess the cardiopulmonary function and aerobic endurance, a chair sit-and-reach test^[52,53]^ to assess lower body flexibility, a back scratch test^[54]^ to assess upper body flexibility, and a time-up-and-go test (TUG)^[53,54]^ to evaluate dynamic balance and agility.Advice: A set of rehabilitation exercises will be taught, including breath adjustment, posture adjustment, guidance for contracting abdominal muscles and pelvic floor muscles, head and neck stretching, back scratching, sitting forward stretching, sitting elastic belt assisted upper limb movement, heel lifting and stepping. Each participant will be given a sports manual with exercise instructions and safety information. During the period of hospitalization, all training sessions will be carefully supervised by a rehabilitation physician experienced in therapeutic training. Participants will perform 3 to 20 repetitions for each exercise and 3 to 5 times per week for 12 months, and accurately record the frequency, time and feelings concerning exercise each week, gradually increasing to the maximum tolerance and safety intensity. Participants will also be encouraged to exercise on their own and walk for a few minutes each day.3.Multi-drug evaluationAssessment: Medication appropriateness index (MAI),^[55]^ review of the type, measurement and quantity of drugs used by patients during hospitalization.Advice: Pharmacists will participate in the administration of drugs to the participants, potentially harmful drugs or doses will be revised and patients will receive instructions concerning medication when discharged.4.TCMAssessment: TCM physicians will comprehensively and systematically assess the participants based on the TCM theory of syndrome differentiation, including a TCM tongue diagnosis and pulse diagnosis.Advice: TCM physicians will deliver guidance on performing acupoint massage related to constipation and insomnia, including Zhigou, Zusanli, Dachangshu, Neiguan, Shenmen, and Sanyinchiao. Each participant will be instructed on 0 to 4 related acupoints, and each acupoint will be massaged for 5 minutes every day.5.Patient educationNurses will issue a patient education manual to each participant, covering the basic introduction of frailty, fall prevention education, first-aid knowledge and cardiovascular medicine guidance. All participants in both groups will undergo routine management.

### Follow-up

2.7

Data will be collected from all participants at 4 points throughout the study: before the intervention and 3, 6, and 12 months after the enrollment. Brief telephone reviews will be conducted approximately 2 to 3 times per month for all participants to promote adherence to the intervention. Participants in both groups will receive at least 12 months of telephone follow-up after the completion of the assessment or intervention in order to assess the durability and sustainability of any influence identified once the intervention stops.

Participants in the intervention group will be defined as treatment-compliant if they complete at least 50% of the planned rehabilitation exercises and/or 50% of their planned nutrition guidance program and 50% of the acupoint massage prescribed by TCM within 12 months. Participants will be required to make records in the debilitating record book. The individual dietary plan, rehabilitation exercise instruction with pictures and safety information, medication instruction, diagram of acupoint massage and patient education manual will also be represented in the record book in order to increase patients compliance. Researchers will assess the actual completion through the above requirements at the end of the intervention.

### Statistical management and analyses

2.8

Statistical management: EDC will be established for standardized management. All data of the participants can be traced back to the source. Peking university clinical research institute will mainly participate in the process of establishing EDC, data statistics and quality control of the trial. Full-time supervisors will examine the whole process of the trial. We will regularly publish the research progress and resolve issues in the research.

Statistical analyses: We will conduct an intention-to-treat (ITT) analysis for the primary analysis, including primary and secondary outcomes, with a per-protocol (PP) analysis used for the sensitivity analysis. The ITT population is defined as all randomized participants in the study, and the PP population is defined as all randomized participants who were actually compliant with their treatment. The participants clinical features will be compared between the intervention and control groups. Continuous variables will be expressed as the mean ± standard deviation in a normal distribution and median and interquartile range in a non-normal distribution, and categorical variables will be expressed as numbers and percentages. Baseline characteristics will be compared by χ^2^ tests or Fishers exact tests for categorical variables and *t*-tests or Wilcoxons rank sum tests for continuous variables. A covariance analysis will be used to analyze the Fried phenotype, SPPB and modified means of the 2 groups, taking the central effect of the test into account, and the 95% confidence interval (CI) of the difference between the 2 groups will be calculated. Only when the above 2 main indicators satisfy the statistical hypothesis (superior effect), can the hypothesis be considered valid. For time-event data, the Kaplan–Meier method will be used to estimate death, non-elective hospital readmission and fall events. A log rank test will be performed for the 2 groups. A Cox proportional-hazard regression model will be used to calculate the effect of potential risk factors on the events. We will summarize the number of enrollments and completion of each center, list the drop-outs, compare the total drop-out rate and list the reasons for termination in detail and compare the characteristics between those with missing outcome data and those who have completed follow-up. The safety evaluation table will be included to describe the number of adverse events and the incidence of adverse events, serious adverse events, adverse reactions and serious adverse reactions in the two groups. Statistical significance will be set at a 2-sided *P* value <.05.

A cost-effectiveness analysis will also be performed to determine whether or not CGA and multi-disciplinary management interventions are cost effective relative to no intervention. The costs of outpatient visits, readmissions and delivering the intervention; the type of hospital admission and number of hospitalization; and the length of stay in the hospital within 12 months will be estimated from the perspective of the medical insurance institutions. The number of assessors and interveners, working hours, labor costs, equipment costs and consultation expenses will be obtained. A standard multiplication model will be used to estimate the QALYs, calculated based on the EQ-5D or BADL for each individual using the monthly interval.^[37]^ We will estimate life-years (LYs) using individual patient data by calculating the time to death from recruitment.^[37]^ Costs and QALYs or LYs will be summed as a decision model to estimate incremental cost-effectiveness ratios.

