#### Outline

2.5.1

In this study, 320 elderly participants ≥70 years old will be randomly divided into the intervention group and control group. The intervention group will be given a routine diagnosis and treatment, a CGA and multi-disciplinary management for 12 months, and the control group will be followed up for 12 months with routine management for basic diseases. A flowchart of the trial is shown in Figure 1.

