#### Recruitment process

2.5.2

A schematic overview of the outcomes, measures and timeline is shown in Table 1. The researchers will recruit participants who meet the inclusion criteria and do not meet the exclusion criteria from Beijing Hospital, PLA General Hospital and Tsinghua Changgeng Hospital.

**Table 1 T1:** Schedule of enrollment, interventions, and assessments.

	Visit 1	Visit 2	Visit 3	Visit 4
Time (months ± days)	**0** ± **5**	**3** ± **14**	**6** ± **30**	**12** ± **30**
Consent	√			
Inclusion/Exclusion Criteria	√			
Randomization	√			
Clinical Evaluation				
Demographic data	√			
Medical history	√			
Physical examination	√	√	√	√
Related auxiliary examination (±days), including routine blood test (±7), blood biochemical (±7) D-dimer (±7), NT-pro-BNP (±7), 25-OH-VD3 (±7), hsCRP (±7), thyroid function (±30), echocardiogram (±30).	√		√	√
CGA^∗^	√	√	√	√
Multi-disciplinary Management^∗^	√	√	√	√
Primary Outcomes		√	√	√
Secondary Outcomes		√	√	√
Adverse Event	√	√	√	√

All participants will receive a clinical evaluation by a nurse. Data on sociodemographic characteristics will be collected, including age, sex, marital status, educational level, smoking and alcohol consumption, and living arrangement. The health condition will be assessed by recording the number of comorbidities, fall occurrences in the past, sleeping quality (Pittsburgh sleep quality index [PSQI]),^[41]^ functional status (BADL, instrumental activity of daily living [IADL]),^[42]^ simple nutritional status (diet, appetite, and calf girth), physical activity or exercise, results of a special physical examination, psychosocial components (mini-mental state examination [MMSE],^[43]^ hospital anxiety and depression scale [HADS-A]),^[44]^ geriatric depression scale [GDS-5 items]),^[45]^ and related auxiliary examination (Table 1).

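### QALYs may be taken from EQ-5D or from BADL, which has no stated utility mapping, and a baseline EQ-5D is not clearly scheduled

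*Protocol article*

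**What the plan says.** **Source of the QALYs.** Section 2.1 introduces QALYs, from a multiplication model, "which are calculated based on the EQ-5D or BADL". Section 2.8 repeats this in the cost-effectiveness paragraph: "calculated based on the EQ-5D or BADL for each individual using the monthly interval". Neither place says which instrument takes precedence.

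**The two instruments.** Section 2.1 describes them differently. For EQ-5D, "index values range from 0 to 1, with higher scores indicating a better quality of life". The other is "disability, which is assessed by basic activities of daily living (BADL: total score 6"). No conversion of BADL to a utility appears in the article.

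**Timing.** Section 2.7 says data are collected "at 4 points throughout the study: before the intervention and 3, 6, and 12 months after the enrollment". In Table 1 the secondary-outcome row, which covers EQ-5D, is ticked at Visits 2, 3 and 4 but not at Visit 1. The baseline evaluation in section 2.5.2 names "functional status (BADL, instrumental activity of daily living [IADL"]) along with PSQI, MMSE, HADS-A and GDS. It does not name EQ-5D, and neither does the assessment content in section 2.6.

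**Comparator.** Section 2.8 asks whether the interventions "are cost effective relative to no intervention", whereas section 2.5.1 says "the control group will be followed up for 12 months with routine management for basic diseases".

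**The concern.** A QALY is time multiplied by a preference-based weight, on which 0 stands for death and 1 for full health. The EQ-5D index is meant to supply such a weight. A count of basic activities does not supply one unless a mapping is specified. By offering the two as alternatives, the protocol permits a QALY that is not one. It also leaves open the denominator of the cost-per-QALY ratio.

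The second issue is the starting point. The area under a utility curve over 12 months needs an opening value, and a comparison of QALYs between arms should be adjusted for baseline utility so that a chance imbalance at entry is not read as an effect. Of the two instruments offered, the only one named at baseline is the one that is not a utility.

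The stake is the economic conclusion, not the efficacy conclusion. Fried phenotype and SPPB remain the primary outcomes whatever is done here. But the Discussion calls cost-effectiveness the focus of the research and key to whether its results can be taken up widely. A baseline EQ-5D that was not taken cannot be collected later, and section 3.1 reports that recruitment is under way.

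**Working it through.** The article states no utility, QALY, cost or ICER figure, so there is nothing to reproduce. The check compares what the calculation needs with what is scheduled, and then sizes the gaps.

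**1. BADL as the multiplier**

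Input: total score 6 (section 2.1). Formula: QALY = score × years.

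- Raw: 6 × 1 year = 6 QALYs, which is impossible because one year cannot exceed 1 QALY.
- Rescaled to score/6 (my assumption; the article does not propose it): one point held for a year = 1/6 = 0.167 QALY. This weight comes from the length of the scale, not from any valuation of health.

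**2. Area-under-the-curve weights for EQ-5D**

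Input: visits at months 0, 3, 6 and 12 (section 2.7). Each interval contributes (length/12) × (start value + end value)/2.

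| Month | Weight | From |
|---|---|---|
| 0 | 0.125 | (3/12)/2 |
| 3 | 0.250 | (3/12)/2 + (3/12)/2 |
| 6 | 0.375 | (3/12)/2 + (6/12)/2 |
| 12 | 0.250 | (6/12)/2 |
| Sum | 1.000 | |

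With visits at 3, 6 and 12 only, as ticked in Table 1, the weights are 0.125, 0.375 and 0.250. They sum to 0.75, so 3/12 = 25% of the year is not covered.

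**3. Does a monthly step need monthly data?**

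Take illustrative utilities of 0.60, 0.65, 0.70 and 0.68 at months 0, 3, 6 and 12 (assumptions).

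- From the visits: 0.125×0.60 + 0.25×0.65 + 0.375×0.70 + 0.25×0.68 = 0.075 + 0.1625 + 0.2625 + 0.17 = 0.670.
- Interpolating linearly to each month and summing 12 monthly trapezoids also gives 0.670.

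The two are identical, so a monthly calculation step can be carried out from the scheduled visits.

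**4. Size of a missing opening value**

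With the same follow-up values, which contribute 0.595, the QALY is 0.595 + 0.125 × (baseline value).

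- Baseline value 0: 0.595. Baseline value 1: 0.720. This is the full possible range on the scale stated in section 2.1.
- Carrying month 3 back: 0.595 + 0.125×0.65 = 0.676, against 0.670 with the assumed baseline of 0.60.

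**5. Size of an unadjusted baseline imbalance**

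Assume the arms differ by 0.05 at entry. Through the opening term alone, the QALY difference moves by 0.125 × 0.05 = 0.006. If a fraction b of the imbalance also persists at the later visits (assumption), the shift is 0.05 × (0.125 + 0.875b):

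- b = 0: 0.006
- b = 0.5: 0.05 × 0.5625 = 0.028
- b = 1: 0.050

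The opening term is therefore minor. The more important reason for a baseline EQ-5D is that it allows adjustment.

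**The case against.** The strongest reply is that the article is condensed. It cites a source for the multiplication model, and a BADL weighting or a rule of precedence may stand there, in the full protocol or in an analysis plan. That is possible and cannot be checked. It does not remove the point, because the article states twice that either instrument may be used, and the only description it gives of BADL is of a disability score. The supportable statement is that no mapping is given, not that none could exist.

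Several stronger readings are tempting, and the document does not support them:

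- **That QALYs need monthly EQ-5D.** The text gives a calculation interval, not a measurement schedule, and step 3 of the working shows that interpolation reproduces the visit-based result.
- **That the ICER cannot be computed.** Cost per QALY can be computed from EQ-5D at the scheduled visits. Section 2.8 also allows life-years, which need only time to death.
- **That baseline EQ-5D is certainly omitted.** Section 2.7 includes a data collection point before the intervention. The primary-outcome row is also blank at Visit 1, although Fried phenotype and ability to complete the SPPB are eligibility conditions. BADL, itself a secondary outcome, is measured at baseline despite the blank cell. Table 1 is thus a poor guide to what is measured at entry. What remains is that Fried, SPPB and BADL each have another place in the text that puts them at baseline, and EQ-5D has none.
- **That the instrument will be picked after the results are seen.** The article does not say when the choice is made, and section 2.5.3 has data analysts blinded to group.
- **That the economic comparator is wrong.** Sections 2.5.1 and 2.6 give controls routine management, and the Discussion compares with the control group. The phrase in section 2.8 is loose wording.

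**Conclusion.** The point holds in a limited form. The protocol permits QALYs from a disability score without a stated utility mapping and leaves the QALY source open. It is also inconsistent on whether EQ-5D, the only utility instrument offered, is taken at baseline.

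The instrument question is the larger of the two. Raw BADL gives impossible QALYs, and a simple rescaling (assumed) would value one point for a year at 0.167 with no preference basis.

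The baseline question is conditional. If EQ-5D is not taken at Visit 1, a quarter of the horizon has no opening value. The direct effect is modest: weight 0.125, or about 0.006 QALY for an assumed imbalance of 0.05. The loss of baseline adjustment could matter more, up to 0.05 QALY if the whole of that imbalance persisted.

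These sizes rest on linear change between visits and on the assumed utilities and imbalance. The document gives no figure with which to replace them. The correction should be made because the protocol itself treats cost-effectiveness as central, but no efficacy conclusion depends on it.

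**What to change.** - **Source.** In sections 2.1 and 2.8, make the EQ-5D index the only source of QALYs and delete the BADL alternative. BADL stays as a secondary outcome for disability.
- **Schedule.** Reconcile Table 1 and the baseline list in section 2.5.2 with section 2.7 by listing EQ-5D at Visit 1 in both arms.
- **Calculation.** State that QALYs are the area under the EQ-5D curve through months 0, 3, 6 and 12, and that the between-arm difference is adjusted for baseline EQ-5D. The monthly interval may stay if it is described as linear interpolation between visits.
- **Comparator.** In section 2.8, replace the reference to no intervention with routine management.

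The cost is a few lines of protocol text and one short questionnaire at Visit 1. Any participants already enrolled without a baseline EQ-5D would need that value imputed, by the same rule in both arms. If it has in fact been collected all along, only the wording changes.
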